## DETAILS OF PRODUCTS

The intervention to be tested in this study is dietary intake of fermentable carbohydrates. The assessments made will not be tests of efficacy but of effects on physiological performance. The products used in this study are Generally Regarded As Safe (GRAS) and are available for general purchase.

### Description

**A.** Maltodextrin, 7 gram serving taken 2 times daily for 7 days. Maltodextrin is a long-chain glucose polysaccharide, marketed by the Hut group, (Northwich, UK). The Material Safety Data Sheet for Maltodextrin lists no known side effects.

**B.** Oligofructose, 7 gram serving taken 2 times daily for 7 days. Oligofructose as Orafit P95® is manufactured, marketed and sold in the EU by Beneo, Germany. It is not considered to have any side effects in the doses proposed.

Both products will have a small amount of Carmine Red food dye - E120 - added to the supplement container. This will be approximately 5 grams of red powder in approximately 200 grams of supplement. Carmine Red is not absorbed by the bowel and has no side effects. It is used as a marker of whole gut transit. Its addition to the supplement will improve masking by making both powders pink, and will aid compliance. Carmine Red is of animal origin and not suitable for vegetarians. A similar process was approved by the University of Nottingham Medical School research ethics committee for the 2013 pilot study (A11072013 SCS MRI).

### Packaging and labelling

Both products will be packaged into opaque plastic containers in the NDDC in a food preparation area by staff suitably trained in food hygiene. A suitably calibrated plastic scoop will be provided. Labelling will be done by an independent member of NDDC or SPMRC staff not otherwise involved in the study who will have access to the randomisation codes.

### Storage, dispensing and return

Both products can be stored at room temperature and will be kept in the NDDC until they are dispensed. Before dispensing and on return containers will be weighed to assess the amount of study product used to allow a calculation of compliance. After return both products are safe to be disposed of in general waste.

### Known Side Effects

Both products are recognised as food additives and are not associated with side effects. More information on Orafit P95® is available at [www.beneo.com](http://www.beneo.com).

## **STUDY DESIGN**

### **Trial Configuration**

This will be a parallel group, double- blind, randomized controlled trial

### **Primary endpoint**

- Percentage change in fasting colonic volume after one week of dietary intervention as measured by MRI

### **Secondary endpoints**

- Change in whole gut transit time (WGTT) as determined by Weighted Average Position Score (WAPS) of MRI transit markers 24 hours after ingestion, after one week of dietary intervention
- Percentage change in fasting colonic gas volume after one week of dietary intervention as measured by MRI
- Change in fasting breath hydrogen concentration after one week of dietary intervention, measured in parts per million
- Change in fasting breath methane concentration after one week of dietary intervention, measured in parts per million

### **Exploratory endpoints**

Biological samples will be collected to allow analysis of the following exploratory endpoints once additional funding has been confirmed.

- Change in urinary metabolite concentrations after one week of dietary intervention
- Change in faecal microbiota concentrations after one week of dietary intervention
- Change in faecal short-chain fatty acid concentrations after one week of dietary intervention

### **Stopping rules and discontinuation**

Given the short time frame of the study there will be no planned stopping rules.

### **Randomisation and Blinding**

Participants will be allocated to a treatment group according to a randomization schedule generated by an independent member of staff at the SPMMRC or NDDC using the online program [www.randomization.com](http://www.randomization.com). Randomization will be 1:1 in blocks of 6 to prevent imbalance between groups.

Participants, investigators and analysts will be blind to treatment allocation until analysis of the primary and secondary endpoints is complete. The intervention supplements are both white powders which are indistinguishable. They will be supplied in opaque containers with the gross weight recorded on the side. Labelling will be completed by members of NDDC/ SPMMRC staff not directly involved with the study.

The code will be kept by the Chief Investigator in a sealed envelope and on a password

protected computer not accessible by the study team. No adverse events directly relating to the study product are expected. Should a serious adverse event occur the intervention will be discontinued without any need to unblind as the supplement will have no bearing on subsequent management.

## **Trial Management**

The trial is not sufficiently big to require a trial Steering Committee or Data Monitoring Committee. The Chief Investigator has overall responsibility for the study and shall oversee all study management.

The data custodian will be the Chief Investigator.

## **Duration of the Trial and Participant Involvement**

### **End of the trial**

The trial is expected to last up to 4 months from initiation to the last visit of the last patient.

The last visit of the last patient will be considered to be the end of the trial. Laboratory and data analysis will continue after this time.

## **Selection and withdrawal of participants**

### **Recruitment**

Healthy volunteers who meet eligibility criteria will be recruited by general advertisement on Nottingham University campuses and through the SPMRC and NDDC databases of healthy volunteers who have expressed a wish to be contacted about further studies. We will approach other university departments e.g. MRC Institute of Hearing Research to ask them to assist with advertising. We will also advertise through our social media presence on Facebook and Twitter e.g. [www.facebook.com/UoN.Gastrointestinal.MRI](https://www.facebook.com/UoN.Gastrointestinal.MRI).

Prospective participants will have the study fully explained and will be given an information sheet to read and retain. It will be explained to the potential participant that entry into the trial is entirely voluntary and that they can withdraw at any time but attempts will be made to avoid this occurrence. In the event of their withdrawal it will be explained that their data collected so far cannot be erased and we will seek consent to use the data in the final analyses where appropriate.

The limited resources of the trial mean that we will not recruit participants who do not understand English. Other exclusions will include those for whom a low FODMAP diet or the supplement would prove difficult because of medical issues or ethical choices e.g. diabetes, veganism.

## **Eligibility Criteria**

### **Inclusion**

- Aged 18 or older
- Able to give informed consent

### **Exclusion**

- Self-declared vegetarian, vegan or kosher/ halal diet who cannot eat carmine red dye
- Pregnancy declared by candidate
- History declared by the candidate of pre-existing gastrointestinal disorder that may affect bowel function
- A positive diagnosis of irritable bowel syndrome based on the Rome III criteria questionnaire
- Reported history of previous resection of the oesophagus, stomach or intestine (excluding appendix)
- Intestinal stoma
- Any medical condition making participation potentially compromising participation in the study e.g. diabetes mellitus, respiratory disease limiting ability to lie in the scanner
- Contraindications for MRI scanning i.e. metallic implants, pacemakers, history of metallic foreign body in eye(s) and penetrating eye injury
- Will not limit alcohol intake to  $\leq 35$  units/ week and  $\leq 8$  units per day during trial
- Unable to stop drugs known to alter GI motility including mebeverine, opiates, monoamine oxidase inhibitors, phenothiazines, benzodiazepines, calcium channel antagonists for the duration of the study (Selective serotonin reuptake inhibitors and low dose tricyclic antidepressants will be recorded but will not be an exclusion criteria)
- Antibiotic or prescribed probiotic treatment in the past 8 weeks
- Inability to lie flat or exceed scanner limits of weight  $<120\text{kg}$
- Poor understanding of English language
- Participation in night shift work the week prior to the study day. Night work is defined as working between midnight and 6.00 AM
- Participation in any medical trials for the past 3 months
- Anyone who in the opinion of the investigator is unlikely to be able to comply with the protocol e.g. cognitive dysfunction, chaotic lifestyle related to substance abuse

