**Version 1.0 16th July 2014**

### BACKGROUND AND RATIONALE

Oligofructose (OF) is a fructose-based oligosaccharide and defined in the EU as a dietary fibre. Enzymatically derived from the longer chain inulin, extracted from chicory, it is commonly used in processed food to improve mouth feel in fat-free products. OF is poorly digested and absorbed in the small bowel so passes to the colon where it is fermented by the bacteria usually resident in the colon, termed the microbiota. Its presence in the colon alters the composition of the microbiota, with reported potential benefits to health, leading to its description as a 'prebiotic'.

Recently, however, such poorly digested carbohydrates grouped together by the term FODMAP (fermentable oligo-, di-, mono-saccharides and polyols) have been proposed to exacerbate symptoms of irritable bowel syndrome (IBS) such as abdominal discomfort and bloating. Dietary exclusion of foods containing FODMAPs, such as wheat, dairy and certain fruit and vegetables, has been proposed as a treatment for IBS, with some evidence to support this. FODMAPs are thought to induce symptoms either by drawing water into the small bowel by osmosis, or through gaseous distension of the large bowel, or a combination of these combined with metabolite effects on motility.

The metabolic products of bacterial fermentation are short-chain fatty acids (SCFAs) and gases, such as hydrogen and methane. All of these can become substrates for growth of other bacteria, leading to a complex ecosystem. The SCFA butyrate provides nutrition to colonic epithelial cells, a phenomenon that has created interest in the role of butyrate, and the microbiota, in colon cancer, inflammatory bowel disease and functional gastrointestinal disorders. Recently butyrate has been shown to influence the development of colonic neurons, with potential effects on colonic motility and transit of luminal contents through the bowel. Thus, there appears to be a potential interaction between the colonic microbiota, complex carbohydrates in the diet and gastrointestinal transit with the suggestion of a possible effect on luminal serotonin levels. It is currently unclear how long a change in diet takes to alter the microbiota, but changes have been observed within a day of radical alteration in carbohydrate content of the diet.

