They will then be offered a standard breakfast with water and be asked to swallow 5 transit marker pills. The marker pills (see picture) are made of polyoxymethylene and are the shape of a size 1 gelatine capsule (20mm by 7mm). They are filled with 0.4 ml of 15µM Gadoteric acid solution and sealed with cyanoacrylate superglue. They have previously been used in studies with healthy volunteers and patients without complication (NRES approvals 10/H0906/50 and 11/EM/0245).

[figure not shown]

Note that up to 6 participants will attend visit 2 at the same time. 3 will take their marker pills between 8.30 and 9.30, and 3 will take them between 9.30 and 10.30 in accordance with the order of MRI scanning the following day.

During the visit participants will take part in a group session of advice on how to follow the low FODMAP diet. This will be led by [name], a registered dietitian trained in the instruction of the low FODMAP diet. Written material, published by Guy's and St Thomas' NHS Foundation trust, will be provided as it would be in clinical practice, on loan. This includes 2 booklets: "Reducing Fermentable Carbohydrates the low FODMAP way" and "Suitable Products for the low FODMAP diet". *Note that participants will not start to follow the low FODMAP diet until after their MRI scan the next morning.*

At the end of the visit participants will take away:

- A 24-hour urine collection bottle containing boric acid, with equipment to allow collection
- A standard packed lunch
- A standard meal for evening consumption

Participants may snack in addition to the meals provided but should use the food supplied for their main meals. They should continue their food diaries until the next morning. After 10pm that night no food should be eaten and only water should be drunk.

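### The probiotic exclusion follows supply route rather than exposure and omits prebiotic supplements, so a participant's baseline can already contain the exposure under test; the expected harm is modest and the fix is cheap

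*Protocol*

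**What the plan says.** The only eligibility criterion on recent manipulation of the gut flora is in Protocol, Eligibility Criteria, Exclusion: "Antibiotic or prescribed probiotic treatment in the past 8 weeks". The inclusion list asks only for adult age and "Able to give informed consent". Neither list mentions purchased probiotics or supplements of oligofructose, inulin or other fermentable fibre.

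Elsewhere the protocol describes such products as biologically active and easy to obtain:

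- Background and Rationale, on oligofructose: "Its presence in the colon alters the composition of the microbiota, with reported potential benefits to health, leading to its description as a 'prebiotic".
- Details of Products: "The products used in this study are Generally Regarded As Safe (GRAS) and are available for general purchase".
- Description: "Oligofructose as Orafit P95® is manufactured, marketed and sold in the EU by Beneo, Germany".

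The primary endpoint is a change from baseline: "Percentage change in fasting colonic volume after one week of dietary intervention as measured by MRI". The baseline scan is at Visit 3 (Day 8), and the text for Visit 2 says "Note that participants will not start to follow the low FODMAP diet until after their MRI scan the next morning".

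**The concern.** An eight-week look-back for antibiotics and probiotics is presumably meant to keep out people whose colonic flora has recently been altered; the protocol does not state the aim. The word 'prescribed' makes the rule depend on how the product was obtained. Healthy volunteers recruited by general advertisement would more plausibly buy a probiotic than be prescribed one.

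The silence on prebiotic supplements touches the intervention itself. A candidate who already takes oligofructose is eligible, and the effect of that intake is then part of the baseline measurement. From Day 8 the low FODMAP diet should end this intake, just as the study supplement begins. The measured change is then a swap (oligofructose arm) or a withdrawal (maltodextrin arm), not an addition to a diet without such a supplement.

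The rule also looks only backwards. The alcohol and motility-drug criteria in the same list cover conduct during the study. The probiotic criterion does not, so a participant may start, stop or continue a probiotic between the two scans. Colonic volume, breath hydrogen and methane, and the stored stool and urine samples are all exposed to this.

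**Working it through.** **Inputs from the protocol.** Pilot effect of oligofructose on fasting colonic volume: +18%. Within-individual coefficient of variation: 17%. Target difference: 15%. Size: 36 complete data sets, 18 per arm. Test: one-tailed, alpha 0.05, between groups.

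**Assumptions not in the documents.** A share f of 5-15% of participants are prior oligofructose or inulin users (36 × 0.05 = 1.8 to 36 × 0.15 = 5.4 people). Their intake is comparable to the study dose and they stop it on Day 8.

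**1. The plan's own figure.** With the 17% used directly as the SD of the change:

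- Log scale (difference ln 1.15, SD √ln(1 + 0.17²) = 0.169): power with 18 per arm is 79.9%, and 80% needs 38 in total, close to the stated 36.
- Percentage scale (difference 15, SD 17): power is 84.2%, and 80% needs 32.

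So 17 is the SD that the plan effectively works with. Whether it is the right SD for a change is a separate matter.

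**2. What a prior user would show.** Let d be the unknown multiplicative effect of the low FODMAP diet, the same in both arms.

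| | Oligofructose arm | Maltodextrin arm | Ratio |
|---|---|---|---|
| Non-user | 1.18d | d | 1.18 |
| Prior user who stops | 1.18d / 1.18 = d | d / 1.18 = 0.847d | 1.18 |

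The ratio between arms is the same for users and non-users, whatever d is. In percentage points, with d = 1 for illustration, the contrast is 18 in non-users and 0 − (−15.3) = 15.3 in users.

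**3. Effect on the between-arm contrast.** With users spread evenly over the arms, the mean contrast is 18 − f × (18 − 15.3) = 18 − 2.7f. This gives 17.9 points at f = 5% and 17.6 at f = 15%.

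**4. Effect on an arm mean.** One user moves an arm of 18 by 18/18 = 1.0 point (oligofructose) or 15.3/18 = 0.85 point (maltodextrin), both downwards. With five users split 3:2, the oligofructose arm falls by 3.0 points and the maltodextrin arm by 2 × 0.85 = 1.7. The contrast moves by 1.3 points.

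**5. Effect on precision.** A shift of s points in a share f adds variance f(1 − f)s². With s = 18, the larger of the two shifts:

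- f = 5%: 0.05 × 0.95 × 324 = 15.4; SD = √(289 + 15.4) = 17.4, a rise of about 3%.
- f = 15%: 0.15 × 0.85 × 324 = 41.3; SD = √(289 + 41.3) = 18.2, a rise of about 7%.

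On the percentage scale, with the 15-point target unchanged, power = Φ(15 / (SD × √(2/18)) − 1.645). This goes from 84.2% to about 82.5% (f = 5%) and 79.7% (f = 15%). If the SD of the change is larger than 17, the relative loss is smaller.

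None of this covers probiotics. The documents give no effect size for them, so their contribution to variance cannot be sized.

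**The case against.** The strongest reply is that the trial does not test what is mainly affected. Assessment of Efficacy defines the primary outcome measure as a difference between arms, and allocation is randomised. A reader might infer that admitting prior users biases the primary comparison. The documents do not support that: such users fall into both arms by chance, the shifts in the two arms have the same sign, and the ratio between arms is unchanged. This part of the objection stands.

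A reader might also infer a substantial loss of power from users who show no difference between arms because they carry on with their own product. On the log scale, power would then fall from 79.9% to 76.3% at 5% of participants and 72.3% at 10%. That needs people to keep taking oligofructose or inulin against the low FODMAP instruction that applies from Day 8, so it is not a fair measure of the harm.

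Three further points carry weight. Baseline is habitual diet by design, and the background section notes that oligofructose is common in processed food, so every baseline holds some fermentable carbohydrate. The +18% comes from an uncontrolled pilot on a normal diet, whereas here the diet's effect is called uncertain and a fall on maltodextrin is expected if the hypothesis is right. And the statement that the products are on general sale shows that volunteers could take them, not that they do.

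Partial safeguards exist, but they do not close the gap. Visit 1 records current medication without naming supplements. The food frequency questionnaire and food diaries may reveal use, and FODMAP intake is compared between groups, but none of these is tied to eligibility. The low FODMAP diet begins after the baseline scan and does not address probiotics. No text tells participants to avoid them.

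**Conclusion.** The gap is real and limited. The criterion separates people by supply route, leaves out the class of product to which the active intervention belongs, and does not extend past enrolment. A prior user's baseline can therefore contain the exposure under test.

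Under the stated assumptions the cost to the primary comparison is an SD of about 17.4-18.2% in place of 17%, and a contrast of 17.6-17.9 points in place of 18. The within-arm changes suffer more, at 0.85-1.0 point per user in an arm of 18. They matter because the primary objective is worded as change from baseline, and because a fall on maltodextrin caused by stopping a personal supplement could be read as an effect of the diet. Breath-gas and microbiota baselines are open to the same contamination, which cannot be sized from the documents. The prevalence of use and the comparable dose are assumptions. This is a worthwhile improvement, not a defect that invalidates the design.

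**What to change.** Delete 'prescribed' and let the criterion follow exposure. For example: *antibiotic treatment, or any probiotic, prebiotic or fermentable-fibre supplement (prescribed or purchased, including oligofructose and inulin), within the existing look-back; or unwilling to avoid these, other than the study supplement, until Visit 5*. The length of the look-back remains for the investigators to set.

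Add one question on such products at Visit 1, next to the medication record.

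The cost is one reworded criterion and one question, with no extra visit or measurement. The downside is that a few otherwise eligible volunteers are excluded.

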### **Expected duration of participant participation**

Each participant will be involved for a minimum of 16 days from enrolment. This may be extended, either for patient convenience or to accommodate bookings on the MRI scanner, with a gap between consent and commencement of the first food diary.

### **Removal of participants from therapy or assessments**

Participants may be withdrawn from the trial either at their own request or at the discretion of the Investigator. The participants will be made aware that this will not affect their future care. Participants will be made aware (via the information sheet and consent form) that should

they withdraw the data collected to date cannot be erased and may still be used in the final analysis.

## **Informed consent**

All participants will provide written informed consent. The Informed Consent Form will be signed and dated by the participant before they enter the trial. The Investigator will explain the details of the trial and provide a Participant Information Sheet, ensuring that the participant has sufficient time to consider participating or not. The Investigator will answer any questions that the participant has concerning study participation. Where consent is obtained by a student investigator they will be directly supervised in the process until the PI is assured of their competence, and then indirectly supervised with help available.

Informed consent will be collected from each participant before they undergo any interventions (including physical examination and history taking) related to the study. One copy of this will be kept by the participant, one by the Investigator, and a third by the SPMARC.

Should there be any subsequent amendment to the final protocol, which might affect a participant's participation in the trial, continuing consent will be obtained using an amended Consent form which will be signed by the participant.

## Study Schematic

[figure not shown] = 24 hour urine collection

[figure not shown]

## Details of Trial Regimen

This study will use a parallel group design with 18 subjects per group.

### Visit 1 (Consent) – Day 0

Visit 1 will take place at the NDDC and last 20-30 minutes. After consent has been obtained participants will be screened against eligibility criteria will be enrolled if they are eligible. An MRI safety screening questionnaire will be completed as part of this process. A record will be taken of height, weight, current medication and any medical conditions and smoking history.

Participants will then fill in a food frequency questionnaire, the Comprehensive Nutrition Assessment Questionnaire (CNAQ), a questionnaire validated in an antipodean population to assess FODMAP content of the diet. This is pilot work to look at the utility of the CNAQ in a UK population.

Participants will then be instructed in how to complete a one week food diary. The first day of the food diary will be designated Day 1. They will also be told how to collect a stool sample.

They will be given to take away:

- A one week food diary based on the EPIC food diary, with guidance
- A stool collection kit including gloves, a cardboard tray and sample pots, with instructions

The stool collection kit has been used extensively in other departmental studies. A microbiology container that meets UN3373B standards for transport (Biobottle™; see picture) will be provided, along with a freezable gel pack. Participants will be asked to freeze the gel pack and collect 3 cherry-sized aliquots of stool from a single motion. This should be done at some point in the two days before Visit 2. Once collected, sample tubes can be put in the Bio-Bottle™ along with the gel pack and stored in the home freezer until visit 2.

[figure not shown]

Participants should not take excessive alcohol during the study and should abstain from alcohol from 8am on Day 6 (48 hours before the MRI scan).

### Visit 2 – Day 7

Visit 2 will take place in the NDDC and last around 90 minutes. Participants will attend around 8.30am, and will fast until they attend except for a small amount of water with essential tablets. They will return their stool samples, which will be immediately transferred to the -80C freezers of the NDDC. They will provide a urine sample which will be spun and frozen. Having emptied their bladders, participants will be asked to start a 24 hour urine collection.

They will then be offered a standard breakfast with water and be asked to swallow 5 transit marker pills. The marker pills (see picture) are made of polyoxymethylene and are the shape of a size 1 gelatine capsule (20mm by 7mm). They are filled with 0.4 ml of 15µM Gadoteric acid solution and sealed with cyanoacrylate superglue. They have previously been used in studies with healthy volunteers and patients without complication (NRES approvals 10/H0906/50 and 11/EM/0245).

[figure not shown]

Note that up to 6 participants will attend visit 2 at the same time. 3 will take their marker pills between 8.30 and 9.30, and 3 will take them between 9.30 and 10.30 in accordance with the order of MRI scanning the following day.

During the visit participants will take part in a group session of advice on how to follow the low FODMAP diet. This will be led by [name], a registered dietitian trained in the instruction of the low FODMAP diet. Written material, published by Guy's and St Thomas' NHS Foundation trust, will be provided as it would be in clinical practice, on loan. This includes 2 booklets: "Reducing Fermentable Carbohydrates the low FODMAP way" and "Suitable Products for the low FODMAP diet". *Note that participants will not start to follow the low FODMAP diet until after their MRI scan the next morning.*

At the end of the visit participants will take away:

- A 24-hour urine collection bottle containing boric acid, with equipment to allow collection
- A standard packed lunch
- A standard meal for evening consumption

Participants may snack in addition to the meals provided but should use the food supplied for their main meals. They should continue their food diaries until the next morning. After 10pm that night no food should be eaten and only water should be drunk.

